**Figure 2 fig2:**
[figure not shown]
Acupoints for the acupuncture and sham control acupuncture groups.

#### Sham control group

2.3.2

Subjects who are assigned to the sham control group will receive placebo acupuncture treatment with a noninvasive placebo needle of sham acupoints (35). The Streitberger needle’s device will be positioned on the skin surface at the target sham acupoints, with its external appearance closely resembling that of genuine acupuncture needles. Upon gentle tapping by the practitioner, the blunt tip will retract into the handle assembly, creating a convincing illusion of needle insertion. This mechanism produces both visual and tactile simulations of skin penetration through apparent shortening of the needle shaft while maintaining complete epidermal integrity through a nonpenetrating design. The Streitberger needle has been widely used in clinical research on placebo acupuncture (36–38), and studies have shown that using this needle in a placebo acupuncture group is reliable for the Chinese population (39). Sham HT 7 is 2 cuns (≈40 mm) lateral to HT 7, and sham KI 7 is 2 cuns (≈40 mm) lateral to KI 7 (Table 3; Figure 2). The purpose of choosing the sham points in this way has been explained in previous similar clinical studies (40); this approach avoids the true acupoints and meridian routes. Choosing sham points close to the true acupoints was conducive to blinding.

### Outcomes

2.4

#### Primary efficacy outcome

2.4.1

The primary efficacy outcome is the change in the Pittsburgh Sleep Quality Index (PSQI) total score from baseline to post-intervention.

#### Secondary efficacy outcomes

2.4.2

##### Subjective efficacy evaluation of insomnia

2.4.2.1

Changes in Insomnia Severity Index (ISI) scores before and after treatment, both within and between groups, served as subjective efficacy indicators for insomnia.

##### Objective efficacy evaluation of insomnia

2.4.2.2

(1) Objective sleep parameters, measured via polysomnography (NIHON KOHDEN, Japan) on the second night, included TST; sleep onset latency; rapid eye movement sleep (REMS) latency; wake after sleep onset; frequency of awakenings; sleep efficiency; number of microarousals; arousal index; and percentages of N1, N2, N3, and REM sleep (N1%, N2%, N3%, R%). Only data from the second night of the monitoring phase were analyzed for efficacy assessment. PSG is resource-intensive and burdensome, requiring overnight laboratory stays, and repeated assessments at multiple follow-up points would increase dropout risk and costs, while possibly introducing practice effects or sleep disturbances from the unfamiliar environment. In contrast, subjective questionnaires (PSQI, ISI) are non-invasive, easily administered remotely, and suitable for repeated measurements. Therefore, PSG was prioritized for pre- and post-treatment assessments to verify immediate physiological effects, whereas subjective scales were used to track longer-term clinical outcomes.(2) Actigraphy (ActiLife, United States), which uses a motion sensor worn on the nondominant wrist to assess body movements, serves as an objective indicator for evaluating sleep–wake states. The changes in the number of awakenings, total wake time (TWT), total sleep time (TST), and sleep efficiency before and after treatment will be measured using actigraphy (41).(3) Fasting venous blood will be collected pre−/post-intervention (08,00–09:00) for serum 5-HT analysis. Changes in these parameters before and after acupuncture intervention will be used to assess objective therapeutic efficacy.

##### Evaluation of emotional state and daytime functioning

2.4.2.3

Changes in the Beck Anxiety Inventory (BAI) and Beck Depression Inventory (BDI) scores before and after treatment will be used to evaluate emotional state, whereas changes in the Fatigue Severity Scale (FSS) and Epworth Sleepiness Scale (ESS) scores will be used to assess daytime functioning.

To address multiplicity while maintaining a clear interpretative framework, three outcomes are prespecified as key secondary endpoints: (1) change in PSG-derived TST from baseline to post-treatment; (2) change in PSG-derived sleep efficiency from baseline to post-treatment; and (3) change in ISI score from baseline to post-treatment. These three endpoints will be subject to formal false discovery rate control. All remaining secondary outcomes are exploratory and will be presented with nominal *p*-values without multiplicity adjustment for hypothesis-generating purposes.

### Safety evaluation

2.5

#### Acupuncture safety

2.5.1

Safety will be evaluated by comparing pre- and post-treatment laboratory results, including complete blood count, liver function tests (ALT, AST), and renal function tests (BUN, Cr).

#### Adverse events

2.5.2

AEs will be recorded and include needle-related reactions such as fainting during acupuncture (needle syncope), a stuck needle (needle retention), subcutaneous bleeding, haematoma, and other unexpected events. AEs will be classified into three severity levels: mild (no impact on normal functioning), moderate (partial impact on normal functioning), and severe (significant impairment of normal functioning). The causality of AEs will be assessed using a four-level classification: definitely related, probably related, possibly unrelated, and unrelated/undetermined. Additionally, a serious adverse event (SAEs) form will be used to document major safety incidents during the trial. In the context of acupuncture, SAEs encompass traumatic pneumothorax, subarachnoid hemorrhage, injuries to the brain, spinal cord, heart, blood vessels, liver, spleen, kidneys, and gallbladder; hepatitis B, hepatitis C, AIDS, syphilis; other severe local or systemic infections; severe neurologic or vascular injuries; permanent disability; and death (42). SAEs will be reported to the principal investigator within 24 h and to the institutional ethics committee within 72 h, with follow-up until resolution or stabilization.

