## Introduction

1

Glucocorticoids (GCs) were first applied clinically by Hench et al. in 1950 for rheumatoid arthritis treatment, earning the Nobel Prize in Physiology or Medicine the following year (1). Despite their widespread clinical use for anti-inflammatory, immunosuppressive, and antipyretic effects, GCs exhibit numerous adverse effects (2, 3), including hypertension, diabetes mellitus, obesity, osteoporosis, and peptic ulcer exacerbation (potentially leading to hemorrhage or perforation) (4), and even cause neurological symptoms. Neuropsychiatric complications may manifest as personality changes, psychosis, or even epileptic seizures (5).

Among these, glucocorticoid-induced insomnia (GII)—characterized by excitation, agitation, anxiety, depression, or mania—represents the most prevalent complication (6). The clinical manifestations of GII include sleep initiation/maintenance difficulties, reduced sleep quality, and decreased total sleep time (TST), warranting clinical attention, as chronic insomnia may exacerbate pre-existing psychiatric symptoms and compromise GCs therapeutic outcomes (7).

To our knowledge, no randomized controlled trial has specifically targeted glucocorticoid-induced insomnia, and current management generally follows established protocols for primary insomnia. Conventional treatments for insomnia include pharmacotherapy (benzodiazepines, nonbenzodiazepine hypnotics, antidepressants, and antihistamines) and nonpharmacological interventions. While rapid-acting, pharmacological options carry risks of hangover effects, cognitive impairment, and dependence (8). Cognitive behavioral therapy for insomnia (CBT-I) and other psychotherapeutic approaches are generally accepted internationally as the primary recommended treatment for chronic insomnia disorder (9). However, due to their time-intensive nature and because physicians need much professional training to conduct them, these methods are not fully implemented in China. Other guideline-endorsed modalities (light therapy, physical therapy, and sleep hygiene education) demonstrate limited efficacy and stability, with the European Insomnia Guidelines rating evidence for light therapy and physical therapy as low quality (10).

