#### Blinding

2.2.6

The allocation sequence is implemented using sequentially numbered, opaque, sealed envelopes prepared by personnel not involved in participant enrolment. Each envelope contains the treatment card corresponding to the next allocation in the sequence. After eligibility is confirmed and written informed consent is obtained, the treating acupuncturist opens the next envelope in numerical order immediately before the first treatment. Envelope integrity and the date and time of opening are documented.

Emergency envelopes labeled with “Emergency Unblinding Document: Clinical Trial of Acupuncture for GII,” containing group assignments (e.g., “Participant ID XXX: [Group]”), were prepared identically to treatment envelopes. Unblinding was permitted only for (1) serious adverse events or (2) life-threatening emergencies requiring immediate intervention, following approval by the principal investigator. Participants with unplanned unblinding will be excluded from the PPS but retained in the FAS and safety analyses.

The database will be locked after blind review and resolution of all data queries. Group allocation will be revealed to the principal investigator and statistician only for the final analysis. Blinding will be considered compromised if full allocation disclosure occurs or if >20% of emergency envelopes are opened during the trial.

This is a single-blind trial with participants blinded to treatment allocation. The acupuncturists are not blinded due to the nature of the intervention. However, all outcome assessors (including those administering the PSQI, ISI, and other questionnaires), PSG scorers, actigraphy analysts, laboratory personnel performing the 5-HT assays, and statisticians are blinded to group assignment until database lock. To assess participant blinding success, a standardized questionnaire will be administered upon completion of the intervention, asking participants to guess their allocated group and rate their confidence. Bang’s Blinding Index will be calculated to quantify the adequacy of blinding. Emergency unblinding is permitted only under predefined conditions (SAEs or life-threatening emergencies) and requires principal investigator approval. Participants with unplanned unblinding will be retained in the FAS and safety analyses but excluded from the PPS as a major protocol violation.

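### The causality scale pools undetermined with unrelated events and has no possibly related grade, and the printed SAE list needs reconciling with the unblinding rule

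*Protocol article*

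**What the plan says.** Section 2.5.2 (Adverse events) of the protocol article sets four rules that matter here.

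- **Recording.** Needle reactions are recorded, and the list ends with an open item: "subcutaneous bleeding, haematoma, and other unexpected events".
- **Causality.** Each event gets one of four grades: "definitely related, probably related, possibly unrelated, and unrelated/undetermined".
- **Seriousness.** A separate form documents major safety incidents. The text then says "In the context of acupuncture, SAEs encompass traumatic pneumothorax, subarachnoid hemorrhage", and goes on to organ injuries, named blood-borne infections, other severe infections, severe neurologic or vascular injuries, permanent disability and death.
- **Reporting.** "SAEs will be reported to the principal investigator within 24 h and to the institutional ethics committee within 72 h".

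Section 2.2.6 (Blinding) gives the triggers for emergency unblinding: "Unblinding was permitted only for (1) serious adverse events or (2) life-threatening emergencies requiring immediate intervention". The principal investigator must approve it.

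Section 2.6.1 (Data sets definition) puts everyone with at least one intervention and recorded safety data into the Safety Set.

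**The concern.** Safety is a declared aim of the trial, and attribution will be hard. Every participant takes systemic glucocorticoids, and the Introduction lists many adverse effects of these drugs, including "peptic ulcer exacerbation (potentially leading to hemorrhage or perforation", psychosis and seizures. Some events will have no clear cause. A scale that files such events with those judged unrelated, and that gives a merely plausible link no related label, leans away from the intervention exactly where judgement is weakest.

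The seriousness definition raises a second question. The 24 h and 72 h duties attach to SAEs. If staff read the printed list as complete, a hospital admission or a life-threatening event outside it could be recorded as an ordinary adverse event and not be sent on within those times.

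**Working it through.** No figure in the article can be reproduced for this point. The check is a reading of the rules against each other.

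**1. Where three kinds of event land on the scale**

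| Assessor's judgement | Grade available |
|---|---|
| Not caused by the intervention | Fourth |
| Cannot be assessed | Fourth |
| Plausible but unproven | None that fits: either up to probably related or down to possibly unrelated |

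The first two rows share a code, so the grade alone cannot separate them later. In the third row, only the first two of the four grades carry a related label. An assessor unwilling to say *probably* must choose a label containing *unrelated*.

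**2. What this does to a count**

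Let R be the events in the two related grades, P those graded possibly unrelated, D those judged unrelated and U those undetermined, with N = R + P + D + U. The form yields R, P and the sum D + U, but not U.

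- Share carrying a related label: R/N.
- Share if undetermined events are counted as related: (R + U)/N, a difference of U/N.
- From the form as printed, U is known only to lie between 0 and D + U. The second share can therefore only be bounded by (R + D + U)/N, which also counts every event judged unrelated.

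The article gives no value or expectation for R, P, D or U, so no number can be put on U/N.

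**3. What depends on the causality grade**

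- Recording of adverse events: no condition on causality.
- SAE reporting at 24 h and 72 h: no condition on causality.
- Membership of the Safety Set: no condition on causality.

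The scale can therefore affect attribution, but not whether an event is recorded or reported.

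**4. The SAE list beside the unblinding rule**

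- The printed list has no item for hospitalisation or its prolongation, and no general item for life-threatening events. Some listed events, such as subarachnoid haemorrhage or traumatic pneumothorax, can be life-threatening, so what is absent is the general criterion.
- The unblinding rule numbers SAEs and life-threatening emergencies as two separate triggers. Read literally, an event can be life-threatening enough to justify unblinding without being an SAE, and so without the 24 h and 72 h duties.
- A perforated ulcer that leaves no permanent disability is an example. It fits no listed item clearly, yet could meet the second unblinding trigger. A seizure is a weaker example, since it might be argued under severe neurologic injuries.

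**The case against.** The strongest reply is that the SAE sentence does not define a closed list. It says that SAEs encompass certain events in the context of acupuncture, and it follows open wording about major safety incidents. A condensed article may well leave general seriousness criteria to the full protocol or the SAE form. Naming life-threatening emergencies separately does not prove that they are not SAEs, and since unblinding needs the principal investigator's approval, cases that require it do reach that person. All of this stands. It reduces the second part of the point to a request to reconcile two sections.

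A reader might infer two stronger claims. Neither is supported.

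- *Harm will be under-reported.* This would require recording or reporting to depend on causality, and step 3 of the working shows that neither does.
- *All non-needling hospital admissions escape expedited reporting.* The list includes severe infections and severe neurologic or vascular injuries, and its wording does not restrict them to needling. A severe systemic infection would be covered even if the list were closed.

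Two further replies have some force. The Introduction describes glucocorticoid risks in general, and the exclusion criteria remove psychiatric system disease and unstable underlying disease, so those risks cannot be carried over unchanged to this sample. The article also defines no related-event rate, and section 2.5.1 describes the safety evaluation through laboratory comparisons. The effect on a published count therefore assumes that events will be tabulated by causality. That is the natural use of a causality grade, but it is not stated.

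None of this answers the point about the scale itself. The four grades are printed in full, so condensation does not explain the pooling or the missing grade.

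**Conclusion.** The point on the causality scale holds on the printed text. Undetermined events cannot be told apart from unrelated ones, and there is no possibly related grade, so treatment-related harm may be under-attributed. The amount is U/N in the notation above and cannot be quantified from the article. It matters only so far as events are undetermined and results are presented by causality.

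The point on seriousness is weaker. The printed list omits hospitalisation and a general life-threatening criterion, and it sits awkwardly beside the unblinding rule. Events would miss the 24 h and 72 h route only if the list is applied as exhaustive and no fuller definition exists elsewhere.

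The primary estimate, the type I error rate, power and the randomised comparison are untouched. What is affected is how far the safety conclusion can be relied on.

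**What to change.** **Causality.** Add a possibly related grade. Make undetermined (not assessable) a category of its own, separate from unrelated, and show it by arm. Add a conservative sensitivity tabulation that counts undetermined events as related. Recruitment is still ongoing and completion is anticipated in December 2026, so the change can protect data not yet collected. The cost is a form change and a slightly less favourable related-event count.

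**Seriousness.** Reconcile sections 2.5.2 and 2.2.6. State that the acupuncture list adds to general outcome-based seriousness criteria: death, life-threatening event, hospitalisation or its prolongation, persistent disability, and other medically important event. The 24 h and 72 h reporting then covers such events whatever their cause. If the full protocol or SAE form already says this, a sentence in the text is enough. Otherwise the cost is a few more SAE reports.

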### Statistical analyses

2.6

Statistical analyses will employ both the full analysis set (FAS) and per protocol set (PPS) approaches.

#### Data sets definition

2.6.1

FAS: All randomized participants who received at least one intervention and had at least one post-baseline efficacy assessment. This set will be considered a modified intention-to-treat (ITT) principle. Participants who experience major changes in glucocorticoid exposure will be retained in the FAS.

PPS: Subjects who met inclusion/exclusion criteria, completed ≥80% of acupuncture sessions, and had no major protocol violations (e.g., unauthorized use of sedative-hypnotic medications). Participants who experience major changes in glucocorticoid exposure will be excluded from the per-protocol set.

Safety Set (SS): All subjects who received at least one intervention and had safety data recorded. Participants who experience major changes in glucocorticoid exposure will be retained in the SS.

Cases with unauthorized use of sedative-hypnotic medications will be excluded from the PPS but retained in the FAS and SS analyses.

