#### Primary and secondary analyses

2.6.2

All statistical tests will be two-sided, with *p* < 0.05 considered statistically significant for the primary outcome. The primary analysis will use a mixed model for repeated measures with PSQI total scores at all post-baseline visits (post-treatment, 1-week follow-up, and 1-month follow-up) as the dependent outcomes. Group, visit, and the group-by-visit interaction will be included as fixed effects, and baseline PSQI score will be entered solely as a covariate. Within-participant correlations will be modeled using an unstructured covariance matrix, and parameters will be estimated by restricted maximum likelihood. The adjusted between-group mean difference at the post-treatment visit, with its 95% confidence interval, is prespecified as the primary comparison; the 1-week and 1-month contrasts are secondary longitudinal comparisons.

For continuous secondary outcomes measured repeatedly, MMRM or generalized estimating equations will be used as appropriate to the outcome distribution and measurement schedule. The primary MMRM will use all available post-baseline observations under a missing-at-random assumption without single imputation. Multiple imputation will be used as a supportive sensitivity analysis, and a delta-adjusted pattern-mixture analysis will assess robustness to departures from the missing-at-random assumption. Major changes in glucocorticoid exposure will be treated as intercurrent events: participants will remain in the FAS and SS and their observed outcomes will be included in the primary treatment-policy analysis, whereas they will be excluded from the PPS. Glucocorticoid dose stability (stable vs. unstable according to the predefined criteria) will be included as a binary covariate in a prespecified sensitivity analysis, rather than in the primary model.

For the three key secondary endpoints (change from baseline to post-treatment in ISI score, PSG-derived sleep efficiency, and PSG-derived TST), the Benjamini-Hochberg procedure will control the false discovery rate at 5%. The remaining exploratory outcomes will be reported with nominal *p*-values without adjustment and interpreted as hypothesis-generating.

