### Quality control and data monitoring

2.7

Study data will be collected at four time points: baseline (1 week before the initial intervention), post-treatment (on the final treatment day), 1-week follow-up (days 6–8 post-treatment), and 1-month follow-up (days 26–36 post-treatment). Data collection will comprise three components: (1) Participants will independently complete standardized assessments at the research centre under supervision, with a dedicated assessment physician available for consultation during the approximately 30-min evaluation period; (2) participants will maintain home sleep diaries for 1 week during each assessment phase under physician guidance; and (3) eligible participants will undergo two consecutive nights of inpatient PSG monitoring before and after the intervention period. At baseline and each follow-up visit, investigators will record the indication for glucocorticoid therapy, underlying disease status, glucocorticoid type, route, dose, timing of administration, treatment duration, dose changes, and concomitant medications with potential sleep effects. Pain intensity, emotional status, caffeine/alcohol use, and sleep diary information will also be collected to assess potential confounding factors.

Dedicated research personnel will receive specialized training in data entry, coding, and secure storage protocols prior to handling study data. Similarly, data analysts will complete comprehensive training in data evaluation and statistical analysis methods prior to performing study analyses.

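### The FAS leaves out participants lost before the final treatment day, so the multiple imputation and delta-adjusted analyses cannot test informative early dropout at the primary contrast

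*Protocol article*

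**What the plan says.** Section 2.6.1 of the protocol article defines the FAS as "All randomized participants who received at least one intervention and had at least one post-baseline efficacy assessment" and adds: "This set will be considered a modified intention-to-treat (ITT) principle". Section 2.6 states: "Statistical analyses will employ both the full analysis set (FAS) and per protocol set (PPS) approaches".

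Section 2.7 sets the schedule. It begins "Study data will be collected at four time points: baseline (1 week before the initial intervention" and continues with "post-treatment (on the final treatment day), 1-week follow-up (days 6–8 post-treatment), and 1-month follow-up (days 26–36 post-treatment". Table 2 agrees: PSQI, ISI, PSG, actigraphy, 5-HT, BAI, BDI, FSS and ESS are marked at week 0 and then not before week 4. Only the sleep diary is marked in weeks 1 to 3.

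Section 2.6.2 models "PSQI total scores at all post-baseline visits (post-treatment, 1-week follow-up, and 1-month follow-up) as the dependent outcomes". Baseline PSQI is a covariate only, and the primary comparison is the adjusted difference at the post-treatment visit. The MMRM assumes data missing at random. Multiple imputation is a supportive analysis, and "a delta-adjusted pattern-mixture analysis will assess robustness to departures from the missing-at-random assumption".

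Section 2.2.3 lists as withdrawals those who refuse further treatment, stop for adverse events, progress, adhere poorly or take hypnotics without authorisation. No outcome visit after withdrawal is described. Section 2.2.4 allows for 20% dropout without saying when it occurs.

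**The concern.** Membership of the FAS depends on something that happens after randomisation: staying long enough to be measured once. With no assessment of a section 2.4 outcome during treatment, that means reaching the final treatment day or attending a later visit. The reasons for leaving earlier (refusal, adverse events, disease progression) may be related to both outcome and arm.

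A delta-adjusted analysis is meant for exactly these participants. If they are removed by definition before it is run, the primary time point is nearly complete by construction, and the analysis will show little sensitivity for that reason alone. A reader of the results could take this as evidence that informative dropout does not matter.

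**Working it through.** **Inputs.** From 2.2.4: 38 per arm, 76 in total, 20% dropout, SD 3.35, expected difference 2.70 PSQI points, two-sided 5% level. The timing of dropout, the share who return after missing the post-treatment visit, and delta are not in the document. They are assumed below and shown over a range.

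**The plan's own figures.** n = 2[(1.960 + 1.282) × 3.35/2.70]² = 32.35 per group, against the stated 31.52, taken as 32. Then 32 × 1.2 = 38.4, stated as 38. These are close enough to use the plan's inputs here.

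**Who is outside the FAS.** The first post-baseline measurement of any section 2.4 outcome is on the final treatment day. Someone who leaves before it and attends neither follow-up has no such measurement and fails the definition. Number excluded = 76 × share lost during treatment:

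- 5%: 3.8, about 4
- 10%: 7.6, about 8
- 20% (all planned dropout falls in the treatment phase): 15.2, about 15

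**Effect of delta if all randomised participants are analysed.** Equal loss in both arms is assumed, with delta applied to acupuncture dropouts only. Shift in the difference = share missing × delta. At delta = 3:

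- 5%: 0.05 × 3 = 0.15 points
- 10%: 0.10 × 3 = 0.30 points
- 20%: 0.20 × 3 = 0.60 points

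**Effect of delta within the FAS.** Post-treatment PSQI can be missing there only for someone who missed that visit but came at 1 week or 1 month. Suppose 20% miss it and a share r of them return. The fraction of the FAS that can be adjusted is 0.20r / [1 − 0.20(1 − r)]:

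- r = 0: nobody, shift 0
- r = 0.10: 1.5 people, 0.02/0.82 = 2.4%, shift 0.07 at delta = 3
- r = 0.25: 3.8 people, 0.05/0.85 = 5.9%, shift 0.18 at delta = 3

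**Tipping point on all randomised participants at 20% loss.** This ignores the added imputation variance and the gain from the baseline covariate. SE = 3.35 × √(2/30.4) = 0.859, and 1.96 × 0.859 = 1.684.

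- Observed difference 2.70: (2.70 − 1.684)/0.20 = 5.1 points
- Observed difference 2.0: (2.0 − 1.684)/0.20 = 1.6 points

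For an observed 2.70, the tipping delta is about 11.1 points at 10% loss and 23.1 at 5%. A result at the planned effect is hard to overturn; one near the significance boundary is not.

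**Effect on the primary MMRM.** None. A participant with only a baseline score contributes no dependent observation, so adding these people to the FAS leaves the MMRM estimate as it is.

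**Consistency with the retention promises.** Section 2.6.1 says that unauthorised hypnotic users and participants with major glucocorticoid changes stay in the FAS. Section 2.2.3 lists unauthorised hypnotic use during treatment as a withdrawal. A participant in either group who leaves before the final treatment day, with no later visit, fails the FAS definition despite the promise.

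**The case against.** The FAS rule asks for an efficacy assessment, not a PSQI score, and Table 2 lists the weekly sleep diary under outcome measurement. If the diary counts, early dropouts who kept it would be in the FAS and could be imputed. This ambiguity is real. But section 2.4 does not name the diary as an efficacy outcome, and 2.7 places diaries in the assessment phases, so the text does not support relying on it.

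A reader might infer that everyone who stops treatment early is lost from the efficacy analyses. The document does not say that. A participant who stops needling but attends any of the three later visits stays in the FAS; the 80% session rule applies to the PPS only. A reader might also infer that about 15 people will be excluded. That needs all 20% dropout to fall before the final treatment day, whereas 2.2.3 also covers losses during follow-up.

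Section 2.6 says both sets will be used, not that no other set may be, and an analysis plan that is not shown could name a wider one. That stands as a caution. Still, the article names no other set for these analyses, and its FAS rule removes the participants they need. It is also fair that the protocol openly calls the set modified ITT, and that only supportive analyses are affected.

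**Conclusion.** The point holds in a limited form. As written, participants who leave before the final treatment day and attend no later visit are outside the FAS, and the stated check on the missing-at-random assumption has almost nothing to act on at the primary post-treatment contrast. At delta = 3 it could move that difference by about 0 to 0.18 points (20% missing the visit, 0 to 25% of them returning). On all randomised participants the shift is 0.15 to 0.60 points, for 5% to 20% lost during treatment. These figures rest on assumed dropout timing, equal loss in both arms and delta in the acupuncture arm only.

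Two stronger conclusions are not supported. The first is that the FAS rule distorts the primary MMRM estimate in a way that a wider set would correct: that estimate is the same either way. The second is that the robustness analysis is empty throughout: those who miss the post-treatment visit and return can be adjusted, and the 1-week and 1-month contrasts can be adjusted for losses after the post-treatment visit.

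This is a should-fix: a stated rule undercuts a stated sensitivity analysis, but the primary result does not depend on it.

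**What to change.** In 2.6.1, define the FAS as all randomised participants, analysed as randomised. At minimum, state in 2.6.2 that the multiple imputation and delta-adjusted analyses use all randomised participants. Impute missing post-treatment PSQI from arm, baseline PSQI and baseline glucocorticoid variables, apply delta to the imputed values, and report the tipping point. Keep the MMRM as the primary analysis.

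Also state that the weekly sleep diary does not by itself qualify as an efficacy assessment. Reconcile the promise in 2.6.1 to keep unauthorised hypnotic users in the FAS with their listing as withdrawals in 2.2.3.

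The cost is wording, slightly more programming and a possibly less favourable sensitivity result. The baseline data needed are already collected. Recruitment is ongoing and the allocation list is held back until database lock, so the change can be made before unblinding.
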